### 4.4 Blinding

Treatment allocation will not be disclosed to participants, study staff, treating clinicians or investigators. The code will only be broken in cases of extreme emergency (refer to 4.5).

The drug manufacturer will ensure study drug and placebo appear identical in regards to appearance, smell and taste. All medication will then be secondary packaged and dispensed in blinded packaging on a per participant basis by a contracted third party pharmacy, according to the treatment allocation derived from the randomisation schedule (refer to 4.6).

Each medication will be numbered according to the pre-determined allocation code and labelled as: '*No. 044/21 Anamorelin (100 mg), placebo. Take one capsule every morning one hour prior to the first meal until finished.*'

## **4.5 Unblinding procedures**

The code will only be broken in cases of extreme emergency. Such situations only include where knowledge of the allocation will have consequences for clinical decision making in consultation with the Lead Investigator who will have access to the sealed unblinding schedule. The Lead Investigator, therefore, must be contacted in the first place. Clinical staff will be able to discuss the clinical situation with the Lead Investigator to determine the urgency and need for unblinding and will be informed by the Lead Investigator of the treatment allocation based on these discussions.

If the Lead Study Investigator is unable to be contacted, the ITCC National Manager should be contacted.

The ITCC will monitor real time unblinding frequency by collecting eCRF withdrawal data and unblinding reporting from the Lead Study Investigator.

## **4.6 Drug supply**

The drug manufacturer will provide the bulk tablets (active and matching placebo). A licensed local pharmaceutical development and manufacturing organisation contracted by the Sponsor will import and store the bulk supply. This will be made available on a Just-in-Time basis to their sub-contracted central pharmacy (referred to as third party pharmacy) for the dispensing activity. The third party pharmacy will secondary package the bulk tablets into study medication kits (90 tablets/kit for the first 12 weeks of treatment period and 80 tablets/kit for the extension phase). The third party pharmacy, will dispense the study medication on a per participant basis upon receipt of a valid prescription. A log will be maintained of the kit dispensed to each participant.

All medications must be dispensed in accordance with the Just in Time delivery system used within the third party pharmacy. The third party pharmacy will dispense the study medication directly to the participant at their home on a per participant basis. The third party pharmacy will retain the randomisation and investigational product dispensing and accountability responsibilities.

## 4.7 Drug accountability and destruction

All active medicine and placebo must be stored in a locked medicine cabinet at or below 25°C within the pharmacy. The pharmacy will maintain accountability records appropriate to State regulations, in addition to the study allocation records.

Participants will be instructed to bring their diary to each study visit during the treatment period for a compliance/accountability check. Compliance will be assessed at visits at weeks 4, 8 and 12 (plus 18 and 24 for those in the extension phase) using participant record of self-administration (i.e. participant diary) OR counting of the remaining tablets at treatment cessation, if the information has not been recorded in the participant diary. A participant will be considered to be compliant with investigational medication if she/he takes all study drugs provided. If participants have missed any doses, irrespective of the number of doses missed, they will be instructed to not catch up the missed doses if the missed dose was more than 8 hours earlier, but to continue taking on the next day of treatment.

After the last dose is taken and study medication is ceased, participants will return all unused study medication to the contracted licensed pharmaceutical development and manufacturing organisation using the return-addressed satchel provided to the patient with the dispensed drug. Upon receipt of the unused study medication, final accountability will be completed and documented in the study pharmacy records.

All unused study medication will be destroyed in a manner consistent with the applicable regulations governing destruction in each state or country. The contracted licensed pharmaceutical development and manufacturing organisation Standard Operating Procedures and state regulations are to be referred to and adhered to at all times.

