## Endpoints and assessments

### Primary - Feasibility

Progression criteria to a Phase III study will be assessed using an indicative traffic light system (green, orange red) whereby green (go) suggests that the criteria have been met and the trial should proceed, orange (amend) indicates that some changes should be made to the larger trial and red (stop) indicates that a larger trial should not proceed. Feasibility in this trial is related to:

- recruitment rate, defined as an average of one participant per site (six sites) every six weeks – plan to recruit 50 participants;
- proportion of participants with complete primary endpoint data – >70% (green), 60-70% (orange), <60% (red);

- participant adherence to investigational medication – >70% (green), 60-70% (orange), <60% (red);
- participant adherence to physical activity advice, as measured by the Short Questionnaire to Assess Health Enhancing Physical Activity (SQUASH), completed at every visit (whereby increase in physical activity will be reviewed over the study period – >40% (green), 30-40% (orange), <30% (red);
- participant adherence to dietary advice, as measured by the food diary kept for three days prior to visits (whereby increase in macronutrient intake will be reviewed over the study period – >40% (green), 30-40% (orange), <30% (red).

**Primary - Desirability:** The study will be considered desirable if there is sufficient signal in the efficacy evaluation to suggest that an adequately powered study would deliver a clinically meaningful difference between groups (where the primary measure has a minimum clinically important difference pre-defined), feasibility endpoints are met and participants find the study acceptable.

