## 3.0 STUDY DESIGN, SETTING AND POPULATION

### 3.1 Study design

This is a multi-site, randomised, double-blind, placebo-controlled, parallel arm, fixed dose, phase II study.

A total of 50 participants with SCLC and anorexia will be randomised 1:1 to oral anamorelin HCl 100mg (Group 1 / intervention arm) or placebo (Group 2 / control arm) once daily ( $\geq 1$  hour before first meal of the day) for at least 12 weeks. Study treatment (Day 1) will start as soon as practicable; ideally prior to cycle 1 of chemotherapy and **no later** than one day prior to scheduled date of cycle 2 of planned chemotherapy. If chemotherapy is not planned, Day 1 should occur within three weeks of screening visit. . At the end of the 12 weeks, participants are invited to enrol in an extension phase where they will continue to receive blinded intervention medication for another 12 weeks. The optional extension (weeks 13-24) is entirely based on participant's preference.

All participants will receive standard physical activity and diet advice leaflets from the study nurse as part of a multi-modal intervention at baseline.

Participants will visit the study centre at baseline, weeks 4, 8 and 12 (plus 18 and 24 for those in the extension phase). During the visits, the study nurse will take the measures and assessments. Primary and secondary efficacy analysis will be conducted at 12 weeks. Additional exploratory efficacy and safety analyses will also be conducted at 24 weeks (for those who opt into the extension phase) in order to collect data over longer treatment duration.

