## 4.2 Dosing schedule

The first day of dosing will be Day 1. The intervention will be delivered as one blinded tablet: one anamorelin HCl 100 mg tablet or one matching placebo tablet. Tablets of study drug are to be taken orally, once daily by the participant in mornings while fasting at least 1 hour before the first meal of the day. Water is permitted prior to and with study drug. Participants will take the first dose of intervention on Day 1, which is the day after receipt of the medication. If a fasting state is not possible on Day 1, participants will start study drug on the next possible day and daily thereafter until Week 12 or up to week 24, if a participant opts in for blinded continuation in the extension phase. If participants have missed any doses, irrespective of the number of doses missed, they will be instructed to not catch up the missed doses if the missed dose was more than 8 hours earlier, but to continue taking on the next day of treatment. Participants will be supplied with study drug within business days after randomisation (i.e. up to one day prior to starting Cycle 2 of chemotherapy) and at Week 18.

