### **Change #10**

•4.6 Drug supply– Detailed information on drug supply and external pharmacy were included in the protocol. In addition, the number of tablets/kit have been updated to allow for variances in days until study Visit 5 when participants will decide if they want to participate into the extension phase.

*“The drug manufacturer will provide the bulk tablets (active and matching placebo). A licensed local pharmaceutical development and manufacturing organisation contracted by the Sponsor will import and store the bulk supply. This will be made available on a Just-in-Time basis to their sub-contracted central pharmacy (referred to as third party pharmacy) for the dispensing activity. The third party pharmacy will secondary package the bulk tablets into study medication kits (90 tablets/kit for the first 12 weeks of treatment period and 80 tablets/kit for the extension phase). The third party pharmacy, will dispense the study medication on a per participant basis upon receipt of a valid prescription. A log will be maintained of the kit dispensed to each participant.”*

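### Section 4.7 requires all supplied drug to be taken, yet the kit holds 90 tablets for 84 doses and the adherence criterion states no unit, so perfect dosing can score red or green

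*Supplement*

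**What the plan says.** Section 4.7 holds the protocol's only definition of compliance: "A participant will be considered to be compliant with investigational medication if she/he takes all study drugs provided". The same section assesses compliance at each treatment visit from the participant's diary. It falls back on a tablet count at cessation if the diary was not kept, and it has participants send back whatever is left after the last dose.

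Section 4.6 sets the supply at "90 tablets/kit for the first 12 weeks of treatment period and 80 tablets/kit for the extension phase". Section 4.2 sets the schedule: "The intervention will be delivered as one blinded tablet: one anamorelin HCl 100 mg tablet or one matching placebo tablet", and "Tablets of study drug are to be taken orally, once daily by the participant in mornings", continuing "daily thereafter until Week 12 or up to week 24, if a participant opts in for blinded continuation in the extension phase". Section 3.1 describes treatment as lasting "for at least 12 weeks". The label text in section 4.4 tells the participant to continue until the supply runs out. The amendment log explains the supply figure: "the number of tablets/kit have been updated to allow for variances in days until study Visit 5".

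The Trial Summary lists the progression criterion as "participant adherence to investigational medication – >70% (green), 60-70% (orange), <60% (red", and section 5.1.1 item 3 repeats the bands. Red is defined there as meaning that a larger trial should not go ahead. Neither place refers to section 4.7, says what the percentage is a percentage of, or gives a denominator.

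**The concern.** The compliance rule is tied to the quantity supplied, and that quantity deliberately exceeds the scheduled doses. A participant can follow the dosing schedule exactly and still fail. The rule is also yes/no with no tolerance, while sections 4.2 and 4.7 tell participants not to make up a dose missed by more than 8 hours. One such miss fails a participant for good.

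This matters because medication adherence is one of five primary feasibility criteria with a go/amend/stop reading. If the criterion is scored with the 4.7 definition, a well-taken drug could be reported as a reason not to run phase III. If it is scored on doses, the same data would be reported as a go. Nothing in the text settles which, so the choice could be made after the data are seen.

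**Working it through.** **Inputs.** One tablet per dose, once daily, to Week 12 (section 4.2). Kits of 90 tablets for weeks 1–12 and 80 for the extension (section 4.6). 50 randomised, with Week 12 data planned on 40 (section 10.1). Bands above 70%, 60–70% and below 60% (section 5.1.1).

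**Supply against schedule**
- Weeks 1–12: 12 × 7 × 1 = 84 doses; 90 − 84 = 6 tablets over; 84/90 = 93.3%. The schedule alone does not give 90. The amendment log calls it an allowance for visit timing but gives no number of days, so 90 cannot be derived and is not itself an error. The whole kit is used only if daily dosing runs to day 90.
- Extension: 84 doses against 80 tablets, 4 short; 80/84 = 95.2%. Both kits together: 170 tablets against 168 doses, 2 over.

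**Same data, three readings.** All 50 participants take every dose and stop at day 84:

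| Reading of the criterion | Score | Colour |
|---|---|---|
| Participants meeting 4.7 literally | 0/50 = 0% | red |
| Tablets taken / tablets supplied | 84/90 = 93.3% | green |
| Doses taken / doses scheduled | 84/84 = 100% | green |

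**The softer reading, no scheduled dose missed.** Assume every participant has the same daily adherence p and that misses are independent. The expected share who comply is p^84. With 50 participants, avoiding red needs at least 30 compliant and green needs at least 36.

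| p | p^84 | P(at least 30 of 50) | 0.8 × p^84 |
|---|---|---|---|
| 0.98 | 0.183 | about 0 | 0.147 |
| 0.99 | 0.430 | 0.01 | 0.344 |
| 0.995 | 0.656 | 0.84 | 0.525 |

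The last column assumes that the 20% without Week 12 data (1 − 40/50) do not take all doses. Without that loss, an expected share of 60% needs p = 0.60^(1/84) = 0.9939, and 70% needs p = 0.70^(1/84) = 0.9958.

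**Sensitivity to clustering.** There are 50 × 84 = 4,200 scheduled doses; 1% missed is 42. If 10 participants miss about 4 each, the other 40 miss none, and 40/50 = 80% comply. That is green under the strict rule, against an expected 43% under independence at the same overall adherence.

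**The case against.** A reader might infer that the criterion is bound to come out red and so to stop the programme. The documents do not support that, for several reasons.

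- The criterion does not cite section 4.7 or use its term. On a dose basis, perfect dosing is green.
- Section 4.7 reads the diary before any tablet count, checks compliance at weeks 4 and 8 when no kit could be empty, and expects leftovers back. In context, its author may well have meant all scheduled doses.
- The surplus is deliberate, treatment is described as a minimum of 12 weeks, and no Week 12 visit window is given. Some participants could use the whole kit.
- The p^84 figures depend on a common p and independent misses, as the clustered example shows. Section 11.3.4 also allows a dose less than 8 hours late to be taken, so such doses need not count as missed.
- The traffic light is described as indicative, and adherence is one criterion of five.
- No separate analysis plan is shown, and units and denominators are often left to one.

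All of this stands against a certain red. It does not rescue the definition. The diary is only the data source; the standard applied to it is still all drug provided. The reading as no scheduled dose missed remains all-or-nothing. The participant-count reading is also the more natural one: 4.7 classifies individual participants, no other definition exists, and the preceding criterion, on complete primary endpoint data, uses identical bands and is explicitly a proportion of participants. An analysis plan could supply a missing unit, but it would still inherit a protocol definition that conflicts with the protocol's own schedule.

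**Conclusion.** The point holds as a conflict between a stated rule and the schedule, combined with an unstated unit. Read literally, section 4.7 classes a participant who takes all 84 scheduled doses by day 84 as non-compliant, at 93.3% of the supply. Read generously, it gives no tolerance for a single missed dose. Because section 5.1.1 does not say what its percentage counts, perfect dosing to day 84 can be scored anywhere from 0% (red) to 93–100% (green).

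The 0% assumes that the criterion counts 4.7-compliant participants and that everyone stops by day 89 at the latest. The 18%, 43% and 66% assume a common p and independent misses; clustering raises them. It cannot be concluded that the trial will report a stop, only that the colour is not determined by the data under the present wording.

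**What to change.** In sections 4.7 and 5.1.1 item 3 (and the Trial Summary):

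1. Define adherence as doses taken divided by doses scheduled over the 12-week period, from the diary first, with the tablet count as a cross-check.
2. Set a participant-level cut-off before any data are scored. 80% is offered as an example; it has no basis in the documents. It would mean 68 of 84 doses (0.80 × 84 = 67.2). Report the mean percentage of doses taken alongside it.
3. State that the existing bands apply to the percentage of randomised participants who reach the cut-off. With 50 randomised, 36 or more is green, 30 to 35 orange, and 29 or fewer red.
4. State how early cessation and death count. A denominator that ends at cessation would score someone who stops after 3 doses as 3/3 = 100%; the full period gives 3/84 = 3.6%.
5. Base the criterion on weeks 1–12 and report extension adherence separately.

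The sponsor should also reconcile the kit sizes (4.6), the label instruction (4.4) and the dosing duration (3.1, 4.2). Which of these should change is not a statistical matter, and no supply or dosing rule is proposed here.

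The adherence change is wording only and needs no new data. Its cost is that the cut-off and the handling of early stoppers must be decided now.

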## 4.8 Cessation of study drug/intervention

Treatment may be ceased for one of the reasons listed below. A description of the reason behind ceasing the drug will be recorded in the medical record or clinical file as per the site's SOP.

- Reached primary endpoint (12/ 24 weeks).
- Participant request.
- Insertion of tube feeding or parenteral nutrition.

- Unacceptable side effects from study medications (defined by National Cancer Institute Common Criteria for Adverse Events; NCI-CTCAE version 5.0) of grade 3 not resolving with appropriate treatment or any grade 4 or 5 toxicities.
- An AE occurs that, in the opinion of the Investigator, makes it unsafe for the participant to continue in the study.
- Participants who in the opinion of the Investigator are not well enough to continue the study (specific reasons for cessation need to be documented in the data collection worksheet and electronic Case Report Form – eCRF).
- It is inappropriate to continue the study medicine for whatever reason.
- The participant or proxy withdraws their consent for continued administration of the study medication, with or without withdrawing consent from study and all protocol-specified assessments and follow-up procedures.
- The participant dies.
- The participant is lost to follow-ups.
- The Investigator, for any reason, terminates the entire study, or terminates the study for that participant; or the attending physician requests that the participant be withdrawn for any medical reason.
- The Sponsor or the Regulatory Authorities or the Ethics Committee(s), for any reason, terminates the entire study, or terminates the study for this trial site or participant.

If a participant prematurely discontinues treatment with anamorelin/placebo at any time prior to completing the 12-week visit, the Investigator must try his/her best to contact the person for scheduled visits. Every effort will be made to collect data from the protocol-specified assessments. Participants will be asked to continue to participate in the study and complete planned visits up to Week 12 even if they have permanently discontinued treatment with anamorelin/placebo (“retrieved dropout” approach). If participants discontinue study participation at any time, they will be asked if they can participate in one final clinical visit and whether they would participate in a follow-up telephone call seven days later.

## 4.9 Treatment failure

The circumstances listed below will be considered a treatment failure. A description of the treatment failure will be recorded in the medical record or clinical file as per the site’s SOP.

- Adverse events related to the study medicine unacceptable to participant, caregiver or clinician in charge;
- Treatment deemed ineffective by treating clinician, who wishes to use alternative therapy;
- Other situations that may require cessation of study medicine:
  - Extended non-response.

#### **4.10 Stopping rules**

The study will be stopped if treatment failure is considered (refer to 4.9) and new literature indicates findings that can be applied to this question in terms of benefit or side effects, or if reporting of adverse events (AEs) indicate that review of the study protocol is required.

## 5.0 OUTCOMES AND MEASURES

### 5.1 Primary Outcome

#### 5.1.1 Feasibility

Progression criteria will be assessed using an indicative traffic light system (green, orange red) whereby green (go) suggests that the criteria have been met and the trial should proceed, orange (amend) indicates that some changes should be made to the larger trial and red (stop) indicates that a larger trial should not proceed. Feasibility will be assessed by evaluating:

1. **Recruitment rate**, defined as an average of one participant per site (six sites) every six weeks – plan to recruit 50 participants.
2. **Proportion of participants with complete primary endpoint data** – >70% (green), 60-70% (orange), <60% (red).
3. **Participant adherence to investigational medication** – >70% (green), 60-70% (orange), <60% (red).
4. **Participant adherence to physical activity advice**, as measured by the Short Questionnaire to Assess Health Enhancing Physical Activity (SQUASH), completed at every visit (whereby increase in physical activity will be reviewed over the study period) – >40% (green), 30-40% (orange), <30% (red).
5. **Participant adherence to dietary advice**, as measured by the food diary kept for three days prior to visits (whereby increase in macronutrients intake will be reviewed over the study period) – >40% (green), 30-40% (orange), <30% (red).

#### 5.1.2 Desirability

The study will be considered desirable if there is sufficient signal in the efficacy evaluation to suggest that an adequately powered study would deliver a clinically meaningful difference between groups (where the primary measure has a minimum clinically important difference pre-defined), feasibility end-points are met and participants find the study acceptable.

### **5.1.3 Efficacy (for clinical assessments)**

1. Change in the 5-item Anorexia Symptom Scale Domain from the 12-item Functional Assessment of Anorexia Cachexia Treatment (FAACT, anorexia/cachexia – A/CS) scale by arm from baseline to week 12.
2. Rates of *on time, on dose* completion of any administered chemotherapy and/or radiotherapy for SCLC during the duration of the study.

